### Analysis of outcome measures

All samples excluding those from patients who withdraw consent will be included in the analysis of outcome measures.

Laboratory data will be analysed using assay-specific software packages employing univariate and multivariate pattern recognition methods (eg, principal component analysis, partial least squares, stochastic neighbour embedding algorithms) between sample groups. Correlation with questionnaire data will allow us to validate prospective markers of disease. In addition, we will use laboratory data to predict disease severity (revised American Fertility Society score^27^), quality of life (EHP-30^20^), pain measures and improvement of symptoms as per follow-up questionnaires. For the multivariate predictive methods, a test set of approximately 30% of each treatment group will be selected at random. This may be selected in a stratified method and exclude patients that have particularly extreme values (eg, >3 SD from the mean). Patients not included in the test set will make up the training set. Models will then be built on the training set and assessed for predictability on the test set.

The final analysis will be performed on the whole data set. However, if some influential differences, for example, in body mass index or comorbidities are seen, then for example, the women with endometriosis will be matched to corresponding women without endometriosis, or women with fibroids to women without fibroids, and the analysis based on these matched pairs.

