### Participants

In each of the disease arms (endometriosis or fibroids), we plan to recruit up to 1200 women of reproductive age (18 years until menopause) who are planned to undergo surgery. Eight hundred of these will have the condition of interest, and 400 will be having surgery for other reasons and act as controls. In addition, we will include fibroid and uterine tissue samples collected as excess tissue (Oxford Radcliffe Biobank, REC Ref 09/H0606/5+5), currently approximately 70 samples.

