### Power calculations

Power calculations were done in R (V.3.6.1) using the *pwr* package. For our primary outcome, we plan to correlate questionnaire and laboratory data. To detect correlations with a moderate effect size of r=0.3 at a power of 80% and 0.05 significance level, we will need 85 samples per group (*pwr.r.test*). For the detection of effect sizes of at least 0.2 between groups (eg, endometriosis cases vs controls, with three cycle phases and five disease stages (0, stages 1–4)) using ANOVA at 0.05 significance and 80% power, at least 32 samples per groups will be used, with a total of 480 samples for all 15 groups (*pwr.anova.test*). Multiple comparisons will be corrected for by Bonferroni’s method.

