## Discussion

This study has been designed to address both uterine fibroids and endometriosis as conditions that both affect the female reproductive system and pose similar problems with regard to pain treatment, fertility and quality of life. By combining the patient collectives into one study, we hope to make use of synergies between the investigations of the two conditions, in addition to the apparent comorbidity between endometriosis patients and those with uterine fibroids.^28 29^ Uniquely, the study protocol allows for the sampling of endometrium on a follow-up visit, which will allow for the assessment of the local, molecular effects of treatment within the same participant.

FENOX has been designed with the EPHect principles^14–17^ in mind to ensure standardisation and reproducibility, and thus should deliver high-quality datasets that will be useful and comparable between centres. We are currently expanding the collection of samples to sites outside of Oxford, with a view to make FENOX a multicentre study within the UK eventually.

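### Judging each predictive model on one random 30% test set is valid but inefficient: resampling all women would cut the variance of the reported performance to roughly a half or a third

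*Protocol article*

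**What the plan says.** The section Analysis of outcome measures describes models that use laboratory data to predict disease severity, quality of life, pain and improvement of symptoms. For these, "a test set of approximately 30% of each treatment group will be selected at random". Then: "Patients not included in the test set will make up the training set", and "Models will then be built on the training set and assessed for predictability on the test set". On how the test set is drawn: "This may be selected in a stratified method and exclude patients that have particularly extreme values (eg, >3 SD from the mean").

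The next paragraph opens: "The final analysis will be performed on the whole data set". It goes on to possible matching of women with and without disease. It does not say whether the predictive models are refitted on all women or how the accuracy of a refitted model would be obtained.

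The section Participants gives the size: in each disease arm "we plan to recruit up to 1200 women of reproductive age", 800 with the condition and 400 controls. The section Power calculations sizes a correlation and an analysis of variance. No section sizes the predictive models.

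**The concern.** Prediction is a declared aim: the secondary objectives include biomarkers and models of disease progression and prediction. The figure a reader will take from such a model is its performance in women it was not trained on. Under the stated plan that figure comes from under a third of the women, scored once, and it depends on which women the draw put in the test set. The model scored is also trained on about 70% of the data.

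If a model is then refitted on everyone, which the whole-data sentence may or may not mean, no test women are left and the article names no other way to measure its accuracy. The published accuracy would then belong to a different model and be less precise than the data allow.

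**Working it through.** **The plan's own figures.** Both power results reproduce. For r = 0.3, two-sided 0.05 and 80% power, the Fisher z method with bias term gives 84.07, rounded up to 85. For 15 groups and an effect size of 0.2, the noncentral F gives 31.36 per group, rounded up to 32, so 15 × 32 = 480 (power 0.810). Neither concerns prediction. They serve below only as illustrative smaller sizes.

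**Inputs from the article.** Test fraction 0.30; up to 1200 women per arm, 800 cases and 400 controls. Test set: 0.30 × 1200 = 360 (240 cases, 120 controls). Training set: 0.70 × 1200 = 840. Accuracy levels, marker counts, effects and N = 170 (2 × 85) are assumptions.

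**Step 1, simple accuracy.** The variance is p(1 − p)/n, so using 0.30N women instead of N multiplies it by 1/0.30 = 3.33 at any p and N. With p = 0.80:
- N = 1200: √(0.16/360) = 0.0211 against √(0.16/1200) = 0.0115; 95% half-widths 4.1 against 2.3 percentage points.
- N = 480: √(0.16/144) = 0.0333 against 0.0183; half-widths 6.5 against 3.6.
- N = 170: √(0.16/51) = 0.0560 against 0.0307; half-widths 11.0 against 6.0.

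**Step 2, AUC.** The Hanley–McNeil variance is [A(1 − A) + (n₁ − 1)(Q₁ − A²) + (n₂ − 1)(Q₂ − A²)]/(n₁n₂), with Q₁ = A/(2 − A) and Q₂ = 2A²/(1 + A). At A = 0.80 the standard error is 0.0228 for 240/120 and 0.0125 for 800/400, a variance ratio of 3.34.

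**Step 3, simulation.** Steps 1 and 2 treat cross-validated predictions as if they came from one fixed model. They do not, so the comparison was simulated.
- *Accuracy, one 10-fold cross-validation.* Linear discriminant, 2:1 cases to controls, 10 or 50 markers of which 5 are informative, total separation 1.0 or 1.8 SD, N = 170, 480 and 1200, 500 replicates each. Hold-out variance was 2.5 to 4.1 times the cross-validation variance. At N = 1200 the SDs were 0.019 to 0.022 against 0.010 to 0.013.
- *AUC, repeated 10-fold cross-validation.* Ridge discriminant, 30 markers of which 6 are real at 0.45 SD. The variance ratio was 2.2 at 85/85 (SD 0.073 against 0.049), 2.5 at 384/96 (the 15-group example: 12 × 32 cases, 3 × 32 controls) and 2.9 at 800/400. Root mean square error against the full-data model at 800/400 was 0.026 against 0.015.
- *A separate AUC run, also under assumed markers and effects.* The ratio was 2.2 to 3.0. At 800/400 the SDs were 0.029 and 0.017, and (0.029/0.017)² = 2.9. The 95% half-widths are 1.96 × 0.029 = 0.057 against 1.96 × 0.017 = 0.033.
- *Continuous outcome among cases*, closer to the severity, quality-of-life and pain targets: ratio 1.8 to 2.5.

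**Step 4, cost of training on 70%.** In the accuracy simulation, the true accuracy of the 70% model fell short of the full-data model by 0.1 to 0.6 points at N = 1200. At N = 170 with 50 markers the shortfall was 2.4 to 3.2 points (0.647 against 0.623; 0.761 against 0.729).

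**The case against.** The best defence is that this is an efficiency preference. A random hold-out is a recognised method and gives an honest estimate for the model that was built. The study calls itself exploratory, its data analysis plan leaves room for further techniques, and a condensed article may leave resampling details to a fuller document. Cross-validation within the training set is not ruled out. At 800/400 the absolute loss is modest. All of this stands, except that the article is not silent: it fixes one random split as the only stated assessment.

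A reader might infer more than the document supports:
- **That 30% of the data is thrown away and the 70% model is the one delivered.** The whole-data sentence prevents that reading. What remains is that no accuracy estimate is provided for a whole-data model.
- **That results are unstable at the plan's own prediction sample size.** The statement that "we will need 85 samples per group" concerns a correlation of 0.3. Smaller prediction data sets are plausible, because some tissues come only from some operations and symptom improvement depends on returned questionnaires, but their sizes are not given.
- **That useful markers will be lost and useless ones kept by the luck of the draw.** The test set is used to assess models. No rule for keeping or dropping markers is stated, and the group comparisons and correlations do not use the split.
- **That the split wrongly claims to show performance outside Oxford.** No such claim is made, and random cross-validation has the same limit. The Discussion says "We are currently expanding the collection of samples to sites outside of Oxford", but describes a multicentre study only as an eventual aim, without numbers or dates.

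The reference to treatment groups, in a study that allocates none, reads as loose wording for the study groups. The option to leave extreme values out of the test set is a separate question, on which this point does not rest.

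**Conclusion.** The point holds as one of efficiency, and of a missing accuracy estimate for any model refitted on all women. It is not a point about validity. Against repeated 10-fold cross-validation, the single 30% test set makes the variance of the reported performance roughly 2 to 3 times larger. The repeated-cross-validation runs span 1.8 to 3.0; the accuracy runs, against a single 10-fold cross-validation, reach 4.1. At full planned recruitment this means an AUC known to about ±0.057 instead of ±0.033. In smaller assay or follow-up subsets the ratio is similar or somewhat lower, but the absolute loss is larger.

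These sizes rest on assumed marker counts, effects and classifiers. The factor 1/0.30 for simple accuracy does not depend on them, but it ignores that resampled predictions come from several models. A better method is available at low cost, so the change is worth making, but leaving the split as it stands would not invalidate the study's conclusions.

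**What to change.** In Analysis of outcome measures, replace the single 30% test set by repeated 10-fold cross-validation or bootstrap optimism correction. Stratify by case/control status where that is the outcome, and otherwise by the outcome being predicted. Repeat marker screening and tuning inside every resample, so that selection is included in the performance estimate. Fit the final model on all women, say so, and report the resampled performance as the estimate for that model.

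The cost is more computing and analysis work, with no additional women, samples or visits. If outside sites do join, a check that holds out whole sites could be added as an option. It is not needed to correct anything the article now says.

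### The plan lets patients with extreme values be left out of the test set but kept in training, so the predictive performance would not represent the study population

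*Protocol article*

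**What the plan says.** All the relevant text is in the protocol article under Analysis of outcome measures. Laboratory data are to be used for prediction: "we will use laboratory data to predict disease severity", and also quality of life, pain and improvement of symptoms at follow-up. The validation design then follows in four steps:

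- The split: "a test set of approximately 30% of each treatment group will be selected at random".
- The option: the draw may be stratified and may also "exclude patients that have particularly extreme values", with more than 3 SD from the mean given as an example.
- The remainder: "Patients not included in the test set will make up the training set".
- The assessment: "Models will then be built on the training set and assessed for predictability on the test set".

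The same section opens with a general inclusion rule: "All samples excluding those from patients who withdraw consent will be included in the analysis of outcome measures". The article does not say whether an extreme value is judged on the outcome, on a laboratory marker, on any of many markers or on a summary score.

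**The concern.** A held-out test set estimates how a model will perform in a population only if it is a random sample of that population. Stratifying the draw preserves this, provided the strata are represented in proportion or reweighted. Removing patients because of their observed values does not. Under the option, such patients have no chance of entering the test set, yet all of them enter the training set. They influence the fitted coefficients, while any error the model makes on them goes unrecorded.

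The general inclusion rule does not repair this. The extreme patients are included in the analysis, but only on the fitting side, and no other sentence in the article provides a held-out assessment of them.

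This bears on a stated aim: the secondary objectives include models of disease progression and prediction. The section on the number of participants stresses how heterogeneous both conditions are, so performance measured without the tails leaves out part of what the models are meant to cover. Because the step is optional and the screened variable is open, the choice could also be made after the data are seen, and it changes the reported result.

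**Working it through.** **The plan's own figures.** The article gives no target for predictive performance and no test-set size, so there is no stated figure to reproduce. The figures under Power calculations concern a correlation and an ANOVA and do not bear on this point.

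**Inputs from the article.** 1200 women per disease arm (800 cases and 400 controls), a 30% test set and an example threshold of 3 SD. The test set is therefore about 0.30 × 1200 = 360 women.

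**Step 1: how many women would be barred.** For one normal variable, P(|Z| > 3) = 0.0027, so 1200 × 0.0027 ≈ 3 women. If a woman is barred when any of k independent normal markers is extreme, the share is 1 − (1 − 0.0027)^k:

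| Markers screened (k) | Share barred |
|---|---|
| 1 | 0.27% |
| 10 | 2.7% |
| 100 | 24% |
| 500 | 74% |

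The values of k and the independence are assumptions; correlated markers would lower the shares. Large k is not far-fetched, because the Assays section plans RNA sequencing and proteomics.

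**Step 2: what this does to measured performance.** The article gives no distributions, no predictor count and no expected R², so these are assumed: n = 1200, test set of 360, linear model, 10 predictors, true R² = 0.30 and 300 replicates. A purely random test set is compared with one drawn only from women within 3 SD, with everyone else in training.

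| Distribution | Exclusion on | RMSE, random | RMSE, trimmed | Change | R², random | R², trimmed |
|---|---|---|---|---|---|---|
| Normal | outcome | 0.841 | 0.832 | −1% | 0.291 | 0.283 |
| t, 4 df | outcome | 0.840 | 0.755 | −10% | 0.292 | 0.314 |
| Lognormal | outcome | 0.832 | 0.663 | −20% | 0.297 | 0.353 |
| Normal | any predictor | 0.843 | 0.839 | −0.4% | 0.290 | 0.287 |
| t, 4 df | any predictor | 0.837 | 0.837 | +0.1% | 0.292 | 0.235 |
| Lognormal | any predictor | 0.839 | 0.843 | +0.4% | 0.291 | 0.183 |

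For example, lognormal with exclusion on the outcome: (0.832 − 0.663) / 0.832 = 20%. In that scenario only 1.5% of women are barred, so a few patients carry much of the error.

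**Step 3: sensitivity to the assumed model.** With a different right-skewed outcome (n = 800, values capped at 150; both the shape and the cap are assumptions), 2.4% of women are barred and RMSE falls from 20.1 to 15.2: (20.1 − 15.2) / 20.1 = 24%. R² falls from 0.19 to 0.08, whereas it rose in the lognormal case above. The fall in prediction error under outcome-based exclusion is consistent across these scenarios; the direction of the change in R² is not.

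**The case against.** The strongest reply is that the default is a random 30% and the exclusion is only permitted. The threshold is an example, the Data analysis plan calls the study exploratory and promises to document the methods used, and neither the case–control comparisons nor the sample size depends on this clause. With near-normal data and few screened variables the effect is about 1%. All of this stands, and it limits the severity. It does not make the option sound: documenting a trimmed test set afterwards does not turn it into a random sample.

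A reader might infer four stronger claims that the article does not support:

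- **That the trimmed test set is simply easier.** This holds for absolute error when outcome extremes are removed. It is not general: R² fell in several scenarios, and exclusion on predictors left RMSE almost unchanged.
- **That the women removed are the most severely affected.** This would follow only if screening were on a right-skewed severity outcome. The variable is not named, and an extreme laboratory value need not mark severe disease.
- **That performance will also be quoted on training women**, because "The final analysis will be performed on the whole data set". That sentence opens a new paragraph and is contrasted directly with an analysis of matched pairs. It most naturally concerns the group comparisons and says nothing about where predictive performance is read.
- **That the test-set figures could not be interpreted at all.** They would describe women within the chosen range, which is a narrower target but one that could be disclosed.

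**Conclusion.** The point holds as a should-fix. As written, the plan permits a test set selected on observed values, sends the excluded women to training and reads performance from what remains. Used that way, the performance figures do not represent the study population. Where the exclusion is on the outcome, prediction error is typically understated, by about 1% for normal data and up to about 20–24% for strongly skewed data. These sizes rest on assumed distributions, a linear model and an assumed R², because the article supplies none of them. R² may move in either direction. The point is confined to the prediction models and to the case where the option is taken up.

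**What to change.** Delete the value-based exclusion from the selection of the test set. Draw the 30% at random, stratified by diagnostic group or disease stage if wished. Set any handling of outliers (for example a log transform, winsorising limits or a robust loss) on the training set alone, and apply it unchanged to both sets. Quote predictive performance from the untrimmed test set. If performance within a central range is of interest, report a trimmed test set as a labelled sensitivity analysis and name the variable and the threshold.

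The cost is a few words in one section, with no extra participants, samples or assays. The one drawback is that the apparent prediction error may look larger.

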#### Secondary objectives

To identify novel biomarkers of endometriosis.To identify clinical subgroups of endometriosis and uterine fibroids.To understand the genetics underlying these conditions and explore the relevant downstream molecular pathways.To investigate the relation between the presence of fibroids and the symptoms, for example, abnormal uterine bleeding.To identify novel drug targets.To develop models of disease progression and prediction.To investigate conditions or symptoms associated with endometriosis and/or uterine fibroids, including: symptoms and characteristics of the female reproductive system (characteristics of menstrual bleeding, fertility, infertility, pregnancy outcomes), pelvic as well as non-pelvic pain conditions, metabolic phenotypes (polycystic ovarian syndrome, obesity and fat distribution), cardiovascular conditions and symptoms, neuroangiogenesis and related neurological symptoms, immunological disorders and cancers.

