### The number of participants

It is now recognised that both endometriosis and uterine fibroids are very heterogeneous conditions. Our previous studies^22 23^ and systematic reviews^24 25^ have clearly identified a lack of sufficiently powered studies. Multiple large-scale research collaborations are currently in place investigating different aspects of endometriosis,^26^ and we plan similar efforts for uterine fibroids. Therefore, large patient numbers are needed.

The Endometriosis CaRe Centre at Oxford is the UK’s largest endometriosis centre. Similarly, as a tertiary referral centre, we see many women with fibroid-associated symptoms. As a result, we have the unique opportunity to collect large amounts of data and samples, which is essential to produce clinically meaningful outputs. Given our current patient recruitment rate (endometriosis: 100/year, uterine fibroids, 200/year), we estimate an enrolment of approximately 2×1200 women over the course of the study (800 endometriosis patients+400 non-endometriotic controls, 800 fibroid patients+400 non-fibroid controls). Fibroids already collected as excess tissue under the Oxford Radcliffe Biobank (REC Ref 09/H0606/5+5) will also be included in this study, currently approximately 70 samples.

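### A data-triggered switch from the whole data set to matched pairs would drop at least 400 of the 800 planned cases per arm, if each designated control is used once

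*Protocol article*

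**What the plan says.** The Protocol article, section Analysis of outcome measures, gives a default and then a condition that overrides it.

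- Default: "The final analysis will be performed on the whole data set". The same section opens by including every sample except those of women who withdraw consent.
- Condition: "However, if some influential differences, for example, in body mass index or comorbidities are seen". What follows is introduced as an example: "the women with endometriosis will be matched to corresponding women without endometriosis, or women with fibroids to women without fibroids". The sentence then ends by moving the result onto that subset: "and the analysis based on these matched pairs".

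The matched analysis is worded as the basis of the analysis, not as a supplement to it. The article does not say what makes a difference influential.

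The group sizes are in two other sections. Participants says of each disease arm: "Eight hundred of these will have the condition of interest, and 400 will be having surgery for other reasons and act as controls". The number of participants repeats this as "800 endometriosis patients+400 non-endometriotic controls, 800 fibroid patients+400 non-fibroid controls".

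The Data analysis plan section already foresees multivariable logistic regression of cases against controls, with adjustment for confounders that suit the hypothesis. It expects age, ethnicity and menstrual cycle phase among them. BMI and comorbidities are not on that list. Secondary objectives includes, among the associated conditions to be investigated, "metabolic phenotypes (polycystic ovarian syndrome, obesity and fat distribution".

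**The concern.** Three features of the rule are troubling together.

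First, the choice between two analysis sets is made after looking at the data, with no stated threshold. Controls are women having surgery for other indications and nothing is randomised, so some difference in BMI or comorbidities is likely. The two sets contain different women and may give different answers.

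Second, the planned ratio is two cases to one control. One-to-one pairing cannot use the surplus cases, so the remedy for imbalance costs patients in a study that justifies its size by the need for large numbers.

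Third, the named triggers are also subjects of the study. If women are matched on BMI, the association of BMI with case status cannot be estimated within the matched set. The rule carries no exception for questions where the matching factor is what is being asked about.

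**Working it through.** **The plan's own figures (Power calculations).**

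- Correlation r = 0.3, 80% power, 0.05 two-sided: n = 84.07, rounded up to 85; power at 85 is 0.804. Reproduced.
- ANOVA with effect size 0.2 and 15 groups: n = 31.36 per group, rounded up to 32; power at 32 is 0.810; 32 × 15 = 480. Reproduced.

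The article gives no figure for a matched-pairs analysis, so the cost has to be derived.

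**Inputs.** 800 cases and 400 controls per arm (Participants; The number of participants). Pairs are read as one case to one control. Assumptions: no replacement, and controls drawn only from the designated 400.

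**Women kept.** Maximum pairs = min(800, 400) = 400.

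- Cases dropped: at least 800 − 400 = 400, or 400/800 = 50%.
- Women dropped: at least 400/1200 = 33%.

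**Precision of a case-control mean difference, in SD units, with unmatched variance.**

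- Whole set: 1/800 + 1/400 = 0.00375; effective size 1/0.00375 = 267.
- 400 pairs: 1/400 + 1/400 = 0.005; effective size 1/0.005 = 200.
- Relative efficiency: 0.00375/0.005 = 0.75.
- Standard error ratio: √(0.005/0.00375) = 1.155.

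**Detectable difference, 80% power, 0.05 two-sided.** The multiplier is 1.960 + 0.842 = 2.802.

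- Whole set: 2.802 × √0.00375 = 0.172 SD.
- 400 pairs: 2.802 × √0.005 = 0.198 SD.
- Power at 0.172 SD falls from 80% to 68%.

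**If not every control finds a match (assumed rates).**

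| Controls matched | Pairs | Cases dropped | Power at 0.172 SD |
|---|---|---|---|
| 100% | 400 | 400 (50%) | 68% |
| 90% | 360 | 440 (55%) | 63% |
| 75% | 300 | 500 (62.5%) | 56% |
| 50% | 200 | 600 (75%) | 40% |

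**When pairing pays for itself.** A paired analysis has variance 2(1 − ρ)/400, where ρ is the within-pair correlation of the outcome. Setting this equal to 0.00375 gives 1 − ρ = 0.75, so ρ = 0.25. Above that, 400 pairs are at least as precise as the unadjusted whole set.

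**Against the plan's cell size.** Four disease stages by three cycle phases make 12 case cells. The mean per cell is 800/12 = 66.7 on the whole set and 400/12 = 33.3 after pairing. The required size is 32, so an uneven stage distribution or incomplete matching would leave some cells below it.

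**The case against.** The strongest reply has five parts.

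- **The control pool is not fixed.** The text speaks of women without the condition, not of the 400 designated controls. The RNA analysis section draws the same broad contrast, so women in the fibroid arm without endometriosis might serve as matches. The Primary outcome section, which speaks of non-affected controls, points the other way. This stands: the loss of at least half the cases rests on an assumption about the pool.
- **The wording is illustrative.** The phrase introducing examples occurs twice, and matching details can be left to a fuller document. This stands in part. Unstated ratios or calipers are no fault here. That the matched pairs become the basis of the analysis is, however, stated.
- **Adjustment does not serve every method.** The section also covers principal component analysis and stochastic neighbour embedding, where a covariate cannot simply be added and balancing the groups is reasonable. This stands and limits the fix.
- **The trigger concerns participant characteristics, not outcomes,** and the Data analysis plan section promises full documentation. This weakens any suggestion of choosing between results. It does not settle which analysis is the main one.
- **The effect is modest.** Four hundred pairs exceed 85 per group, and 800 women exceed 480. This stands at planned recruitment.

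A reader might infer that matching removes a secondary objective by design. The documents do not support that. Secondary outcomes frames the associated conditions as a question about their genetic and molecular basis, not as a comparison of how common they are. Nothing says that matching applies to every question, and an unmatched analysis remains possible.

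**Conclusion.** The point stands as an avoidable weakness of the analysis rule, moderate in size. At 800 cases and 400 controls, with one-to-one pairing, no replacement and only designated controls, at least half the cases in an arm leave the analysis. The information for a case-control comparison falls by at least 25% before any gain from pairing. That gain cancels the loss if the within-pair correlation reaches 0.25 and all controls find a match. A larger control pool would reduce the loss.

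The efficiency comparison is with an unadjusted whole-data analysis. Adjusting for an imbalanced covariate has a variance cost of its own, which cannot be computed from the article.

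A reader might also infer from the recruitment rates that the endometriosis arm will hold 333 cases and 167 controls, where the detectable difference would go from 0.27 to 0.31 SD. That needs 100 women a year for five years, controls counted within that rate, and a 2:1 split. The article does not say that the rate includes controls. The same assumptions for fibroids, at 200 a year, give about 667 and 333. The figure is a scenario and is not used here.

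**What to change.** In Analysis of outcome measures, replace the conditional switch as follows.

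1. For case-control comparisons, the whole-data analysis is the main analysis whatever differences are observed. BMI and relevant comorbidities are listed in advance as covariates beside age, ethnicity and cycle phase.
2. Matching is a sensitivity analysis, or is used for pattern-recognition methods that cannot take covariates. Full or variable-ratio matching is preferable, because it retains cases, and the control pool should be named.
3. A factor is neither matched on nor adjusted for when it is itself the question, for example obesity or polycystic ovarian syndrome.

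The cost is wording and a few more model terms; no data collection changes. The downside is that the main result then relies on the form of the regression model, for example how BMI enters it. The matched sensitivity analysis gives a check on that.
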